## Abstract

Supplemental Digital Content is available in the text

## Introduction

1

### Pain of glossodynia

1.1

“Pain of glossodynia” is persistent and chronic pain that occurs in the mucosal surface of the mouth, and it is the same condition as “burning mouth syndrome.” Because of the name of the disease, it is often referred to as “tongue pain” including intra-oral burning. In the 3rd edition of the International Headache Classification, it is classified as one of the central facial pains and named as an intraoral burning syndrome. According to the 3rd edition of the International Headache Classification, glossodynia is defined as a tingling sensation in the mouth, a tingling sensation, or a tingling unpleasant sensation that recurs for more than 2 hours a day and daily for more than 3 months.

At present, there is no curative treatment for tongue pain because the cause has not been established. Therefore, symptomatic treatment has been used. To date, symptomatic treatments with reported benefits include cognitive-behavioral therapies and topical and oral therapies such as anticonvulsants. Many patients complain of pain during the treatment of glossodynia over a long period; instead of the elimination of pain by the therapies, they end up managing and overcoming the pain that is interfering with their daily life activities.

### Characteristics of the pain of glossodynia

1.2

The pain of glossodynia is all the pain that a patient feels, and it is difficult for others to understand because it is not abnormal even when viewed by others. The degree of pain in glossodynia is sometimes severe and may interfere with work and daily life activities, and necessitate a visit to a medical institution. The nature of the perceived pain may be described as persistent and burning (tingling, tingling) or stinging (tingling, throbbing). It usually lasts from wake-up time to bedtime, but the intensity of the pain has a wave, and it usually does not prevent sleep. Pain is closely linked to psychosocial stress, and anxiety and discomfort at work and home can exacerbate it.

In addition, patients with tongue pain often complain of dry mouth (dryness), which is thought to cause inflammation of the tongue and gingival mucous membranes, worsening the pain. The relationship between taking drugs that suppress oral respiration and the secretion of saliva and stress has also been highlighted, and taste disorders are known as accompanying symptoms. Some case reports revealed that tongue pain was reduced by treating dry mouth.^[1–3]^ Sugiyama et al^[2]^ reported that the symptoms of dry mouth and tongue pain in a 75-year-old male resolved approximately 2 weeks after receiving Goreisan as a treatment for hydrosis when he presented with a chief complaint of dry mouth. Therefore, treating dry mouth may reduce tongue pain.

Various medications such as pregabalin, antiepileptic drugs, duloxetine, amitriptin, antidepressants, N-Methyl-D-aspartate receptor antagonists, and tramadol are prescribed depending on the symptoms of glossodynia. Although pain may reduce, each drug might have side effects, such as drowsiness and dizziness.^[4]^ (II. Pharmacotherapy, CQ8-CQ21, Guidelines for the treatment of chronic pain, 2018)

On the other hand, Goreisan, a Chinese herbal medicine, has already been used by physicians to treat glossodynia and other forms of pain in the oral and maxillofacial regions following weather conditions including change in the barometric pressure. There have been several reports that the administration of Goreisan was effective for pain in glossodynia patients^[5–8]^ caused by acute changes in barometric pressure. Furthermore, large-scale epidemiological studies have shown that pain in rheumatoid arthritis is exacerbated by a weather storm (particularly due to a decrease in air pressure 3 days before the pain test). In the oral and maxillofacial regions, many tissues, including the tongue, are rich in peripheral capillaries and lymphatic vessels and are susceptible to changes in body fluid balance.

As described above, Goreisan may promote the metabolism of tissues such as local mucous membranes, improve stasis, and improve the flow of lymph, which may improve chronic pain. The administration of Goreisan is considered to improve symptoms of the tongue; the tongue is rich in vascular tissue and its symptoms only have few accompanying symptoms of the central nervous system, such as drowsiness and dizziness, and they are associated with a low risk of liver and renal dysfunction. However, as indicated in the latest guidelines for the treatment of chronic pain, the level of evidence for the clinical question, “Is Chinese medicine effective for treating chronic pain?,” remains as 2C to 2D. It is said that no high-quality clinical research has been conducted. In addition, although Kampo medicines are not the same as Western medicines, there is a risk of the side effects of the constituent crude ingredients and cautionary points on interactions with concomitant drugs, and a thorough investigation and a well-designed clinical study are required.

In this study, we will also explore changes in weather (barometric pressure and temperature) that may affect pain perception. Some patients suffering from chronic and persistent pain sometimes complain as follows: “Before it rains, pain in the tongue becomes worse.” The reason for the worsening of pain when the weather changes is not completely understood; it is thought to be caused by a malfunction of sensors that detect atmospheric pressure in the body. Traditionally, oriental medicine has a meteorological medicine sub-field, and when a condition worsens due to a specific weather condition, therapy corresponding to the condition is applied; this has been practiced since ancient times. It is also known that a decrease in barometric pressure exacerbates pain in the trigeminal nerve distributions, including headache in the oral and maxillofacial region and pain in the oral cavity.

It has been suggested that the reason for the worsening of chronic pain caused by meteorological diseases is the activation of the sympathetic nervous system by a signal from a sensor, such as the inner ear, that senses atmospheric pressure. This stimulates stress and causes various diseases. There is also a theory that the pressure of the human body is reduced following the decrease in atmospheric pressure, and the blood vessels easily dilate accompanied by the stagnation of lymph. However, there are only a few basic studies on meteorological diseases and the details are not clear. Sato and colleagues report that changes in the weather associated with a decrease in barometric pressure exacerbate the pain associated with meteorological illness, and they have shown in animal experiments that different neurons in the vestibular nucleus respond to changes in air pressure.^[9]^ A similar mechanism has been observed in humans, and this suggests a link between human meteorological diseases and pain caused by changes in atmospheric pressure.^[10,11]^ If Goreisan can reduce pain in glossodynia patients, it will open up new drug opportunities. There are strong claims that Goreisan is effective for tongue pain, and it cannot be denied that it is one of the effective treatments. However, until now, there is little reliable evidence on the efficacy of Goreisan in reducing pain. In this study, we investigate the tongue pain-reducing effect of Goreisan. In this study, we will also explore the association between the changes in weather (barometric pressure and temperature) and pain. The purpose of this study is to investigate whether Goreisan can reduce pain in patients undergoing treatment for tongue pain. If Goreisan can reduce pain, its candidacy as an alternative treatment for pain in glossodynia can be further supported by more reliable research.

## Methods/design

2

### Study design

2.1

This multicenter, randomized, group-controlled study will involve patients treated for glossodynia. Patients with consent will be randomized and assigned to 1 of 2 groups as shown below (ratio 1:1). In the experimental group, Goreisan will be taken for 12 weeks in combination with conventional treatment, Patients in the control group will only receive the standard treatment (Western medicine administration). The study will be conducted mainly at the Nagasaki University Hospital in Japan. It is registered on the Japan Registry of Clinical Trials. It will also be conducted following the principles of the Declaration of Helsinki and the established best clinical practices of Japan.

### Participant recruitment

2.2

Participants have been recruited from the Nagasaki University Hospital, where the subsequent study will also take place. The treating clinical research coordinator explained the study to all participants, and each participant signed an informed consent form. This is intended for patients undergoing medical treatment with the chief complaint of glossodynia. The medical institutions that will conduct research will target patients undergoing medical treatment at Nagasaki University Hospital (Oral Pain Liaison Outpatient center), Aichi Medical University Hospital, and Tokyo Medical and Dental University. The case registration and allocation organizations are Nagasaki University Hospital, Tokyo Medical and Dental University, and Aichi Medical University; each will perform case registration and allocation using REDCap. REDCap was used to randomly allocate participants to the “Goreisan-administration” and “non-Goreisan-administration” groups at a ratio of 1:1 (stratified block method).

#### Sample size

2.2.1

In this study, ninety patients with the chief complaint of glossodynia undergoing medical treatment are targeted. A preliminary study (Okayasu I. et al, Advances in Traditional Medicine. 2020, In press) found that after 2 weeks of Goreisan administration, the degree of pain on visual analog scale (VAS) was reduced by more than 20%. Improvement was observed in 8 of 14 cases (about 57%). On the rate of pain improvement, the effective rate of the standard treatment group is 10% and the expected effective rate of this drug is 40%, with α of 0.05 and power of 0.9. The number of cases should be approximately 82 (41 in each group) because statistical analysis is possible in approximately 90 cases, in considering a dropout of approximately 10%. Therefore, the sample size is set for approximately 90 cases in total with 45 cases in each group. Each of the 3 medical institutions will be assigned 30 cases (15 cases per group).

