### Statistical analysis

2.11

The difference between the improvement rate between the Goreisan administration group and the non-administration standard treatment group will be analyzed by Fisher exact test. Test the null hypothesis: there is no difference between the rates of improvement of the Goreisan administration group and the standard treatment group.

In addition, the degree of pain will be evaluated using VAS. The verdict for VAS based on subjective symptoms, which is reduced by 20% or more, is “improved,” and the others are “non-improved.” The grounds for improving a VAS that has been reduced by more than 20% from the target value entered by the patient are as follows.

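### The stated 90% power does not match the planned Fisher exact test: read two-sided at 0.05, that test has about 86% power with 41 evaluable patients per group

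*Protocol article*

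**What the plan says.** Section 2.2.1 (Sample size) of the protocol article takes an improvement rate of 10% on standard treatment. For Goreisan and the error rates it says "the expected effective rate of this drug is 40%, with α of 0.05 and power of 0.9". It then concludes: "The number of cases should be approximately 82 (41 in each group) because statistical analysis is possible in approximately 90 cases". Allowing for about 10% dropout, it sets enrolment at about 90, or 45 per group. It names no formula or software, and does not say whether alpha is one-sided or two-sided.

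Section 2.11 (Statistical analysis) says that the difference in improvement rates "will be analyzed by Fisher exact test". The null hypothesis is that "there is no difference between the rates of improvement of the Goreisan administration group and the standard treatment group". This section does not give the sidedness either.

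**The concern.** Power belongs to a particular test at a particular level. Fisher's exact test is conservative: because the outcome is discrete, its actual type I error usually lies below the nominal 5%, and it needs more patients than an uncorrected chi-square test for the same power. A sample size taken from a chi-square formula will therefore usually overstate the power of a Fisher test.

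A null of no difference, with an unqualified 0.05 and no directional hypothesis anywhere in the article, is ordinarily read as a two-sided test. If 41 per group does not give that test 90% power, the plan understates its own false-negative risk even when both assumed rates are correct. A non-significant result would then be weighed against a power that the trial did not have.

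**Working it through.** **Inputs.** From section 2.2.1: p1 = 0.10, p2 = 0.40, alpha = 0.05, power = 0.90, 41 evaluable and 45 enrolled per group. From section 2.11: Fisher exact test, null of no difference. From section 2.2: 1:1 allocation. Sidedness is not stated, so both readings are run.

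**Step 1. Reproduce the plan's figure.** The usual pooled, uncorrected formula per group is

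n = [z_alpha √(2 p̄(1 − p̄)) + z_beta √(p1(1 − p1) + p2(1 − p2))]² / (p2 − p1)²

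Here p̄ = 0.25, so √(2 × 0.25 × 0.75) = 0.6124 and √(0.09 + 0.24) = 0.5745.

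- Two-sided 0.05: (1.960 × 0.6124 + 1.2816 × 0.5745)² / 0.09 = (1.2002 + 0.7362)² / 0.09 = 41.7, so 42 per group. Power from the same formula at 41 is Φ[(0.30 × √41 − 1.2002) / 0.5745] = Φ(1.255) = 89.5%, which is 0.9 to the precision given.
- One-sided 0.05: (1.645 × 0.6124 + 0.7362)² / 0.09 = 33.8. The continuity correction, n/4 × [1 + √(1 + 4/(n × 0.30))]², raises this to 40.2, so 41 per group.
- Two-sided 0.05 with the same correction: 48.1, so 49 per group.

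The plan's 41 therefore fits either the two-sided uncorrected formula (to within one patient per group) or the one-sided corrected formula (exactly). It does not fit the two-sided corrected formula, which is the usual approximation to a two-sided Fisher test.

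**Step 2. Exact power of the planned test.** For every pair (i, j), with i ~ Binomial(n, 0.40) on Goreisan and j ~ Binomial(n, 0.10) on control, compute the Fisher p-value. Power is the total probability of the pairs with p ≤ 0.05.

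| Evaluable, Goreisan/control | Two-sided Fisher, 0.05 |
|---|---|
| 41/41 | 86.4% |
| 41/40 | 87.2% |
| 40/41 | 89.4% |
| 45/45 (no dropout) | 88.9% |
| 46/46 | 89.8% |
| 47/47 | 90.6% |

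The 81-patient rows exceed the 82-patient row because the test is discrete. With equal groups the two-sided p-value is exactly twice the one-sided one; with unequal groups the opposite tail can add less.

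**Step 3. Locate the gap.** At 41/41, by the same enumeration:

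| Test | Power |
|---|---|
| Uncorrected chi-square, two-sided 0.05 | 90.9% |
| Fisher, two-sided 0.05 | 86.4% |
| Fisher, one-sided 0.025 | 86.4% |
| Fisher, one-sided 0.05 | 91.4% |

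The shortfall against 90% is 90 − 86.4 = 3.6 points at 41 per group and 90 − 88.9 = 1.1 points at 45 per group. The type II error at 41 per group is 100 − 86.4 = 13.6%, against the planned 10%.

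**The case against.** The strongest reply is that sidedness is never stated. The one formula that lands exactly on 41 is the one-sided 0.05 continuity-corrected one, and under a one-sided 0.05 Fisher test the power at 41 per group is 91.4%. A reader might infer that the trial simply fails to deliver 90% power. The article does not support that without the condition that the test is two-sided. The reply does not clear the text, though. It would mean that the stated power holds only at a one-sided 5% level that the article nowhere declares, and at the more customary one-sided 0.025 the power is 86.4% again.

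A second reply is that sizing by a standard two-proportion formula and analysing by Fisher is a common approximation, and that the gap is small. This stands as to severity. The mismatch does not touch type I error, bias or the estimate of effect.

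A reader might also infer a dropout error, since 90 × 0.9 = 81 rather than 82, and 82/0.9 = 91.1 rather than 90. The article gives 82, 90 and 10% each as approximate, and going from 90 to 82 is a loss of 8.9%. One patient among three rounded figures is not an error.

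Finally, one might want to recover the 90% by moving to a site-stratified test. Section 2.2 says only that allocation is "at a ratio of 1:1 (stratified block method") and names no stratification factor. Replacing the primary test would also be more than a wording change.

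**Conclusion.** The point holds conditionally. If the Fisher exact test in section 2.11 is two-sided at 0.05, the power of 0.9 in section 2.2.1 is not what that test delivers. Power is 86.4% at 41 evaluable per group, 87% to 89% with 81 evaluable split 41 and 40, and 88.9% with all 45 per group evaluable. The first equal group size to reach 90% is 47. Even full retention of the 90 enrolled patients falls just short.

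This rests on the plan's own rates of 10% and 40%, independent binomial outcomes, and the two-sided reading. It does not rest on any rule for handling dropouts or on doubt about the assumed rates.

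It should be corrected, but it is not a threat to the trial's validity: a shortfall of 1 to 4 points in a planning figure, together with an undeclared sidedness.

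**What to change.** In section 2.2.1, state that alpha is two-sided, name the sample size method, and restate the power for the test that will be used. For example:

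> For improvement rates of 10% and 40%, Fisher's exact test at a two-sided 5% level has about 86% power with 41 evaluable patients per group, and about 89% if all 45 per group are evaluable.

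Section 2.11 should give the same sidedness. If a one-sided 0.05 test was what the plan intended, declare it in both sections, with power of about 91% at 41 per group. The declaration should record the original intention and should not be chosen now to rescue the 90%.

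This is a wording change and needs no extra patients. Its only downside is a slightly less favourable stated power. Keeping 90% with the two-sided Fisher test would instead take 2 × 47 = 94 evaluable patients. At 10% dropout that is 94/0.9 = 104.4, so 105 enrolled, or 106 to keep the groups equal. The size of the gap does not require this.

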### Inclusion criteria

2.3

The following were the inclusion criteria:

(1)Patients undergoing treatment for chronic pain in the oral and maxillofacial region.(2)Age: At the time of obtaining consent, an adult patient who is 20 years or older.(3)Gender: Any.(4)Hospitalization/Outpatient: Outpatient only.(5)Patients who have been given sufficient explanations, have sufficient understanding to participate in this study, and have provided informed consent.

### Exclusion criteria

2.4

The exclusion criteria were as follows:

(1)Patients taking Kampo medicines including Goreisan.(2)Severe hypertension with a diastolic blood pressure of 120 mm Hg or more.(3)Patients with severe liver and renal dysfunction.(4)Patients with drug hypersensitivity.(5)Pregnant women and patients who may be pregnant or lactating.(6)Patients who participated in another clinical study within 4 months.(7)Other patients judged by the investigator to be ineligible as study subjects.

### Study protocol

2.5

Patients who have provided consent should be visited in advance, and the degree of pain and saliva at that time will be assessed. After that, Goreisan will be taken at 7.5 g/d (minute 3) for 12 consecutive weeks. Four weeks later, the patients will return to the hospital for a second assessment of pain and saliva. Eight weeks after this, the patients will be reexamined, and the third assessment of pain and saliva will be performed. Twelve weeks after the first test, a fourth test will be performed.

During each outpatient consultation, the weather conditions, such as temperature, humidity, and barometric pressure, should be recorded and displayed on the outpatient meteorometer on the chart. Patients should also observe, and possibly record, the degree of pain at home, in addition to assessments during their visit to the outpatient clinic at a medical institution (Table 1).

**Table 1 T1:**
[figure not shown]
Research schedle and items.

### Adverse events

2.6

In this study, adverse events related to the study drug (possible liver dysfunction due to long-term use of Goreisan) will be considered. During the study period, blood will be drawn and liver function tests will be performed. If there are any abnormalities, the study will be discontinued immediately and appropriate treatment will be administered.

### Outcome

2.7

The primary endpoint is the 20% or more improvement on the VAS relative to the control value at the outpatient visit 12 weeks after administration based on the self-filled VAS of patients.

(The main evaluation point is the 20% or more improvement in the VAS control value at the outpatient visit 12 weeks after administration.) (All itmes to be collected as listed in SDC).

#### Rationale for an improvement rate of 20% or more

2.7.1

The degree of pain will be evaluated using VAS. Regarding the determination of VAS based on subjective symptoms, those with a decrease of 20% or more are “improved,” and the other cases are “not improved.”

The grounds for improving the VAS entered by the patient by 20% or more are as follows. This criterion was based on previous drug information for celecoxib (KEGG Drug Databese), using the 20% improvement criterion used by the American College of Rheumatology. For this criterion, patients with a 20% or greater improvement in pain perception (VAS) were considered valid cases when assessing the efficacy of celecoxib. In the clinical trial that evaluated the clinical outcomes of celecoxib for rheumatoid arthritis pain, assessments were performed using the American College of Rheumatology improvement rates (various methods), and the results provided drug information for treating patients with a VAS improvement of 20% or more. This standard was adopted for pain improvement following the administration of Goreisan.

#### Secondary outcome

2.7.2

The secondary endpoint is improvement of each item at the outpatient visit at 4 and 8 weeks after Goreisan administration.

(1)VAS evaluation(2)Salivary amylase activity (10–200 kIU/L)(3)Tongue examination (whether the veins on the back of the tongue are angry)(4)Weather information (barometric pressure)

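### Barometric pressure is listed as a secondary endpoint to be improved, although it is an exposure; the clinic-visit readings alone do not measure the short-term pressure change of interest

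*Protocol article*

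**What the plan says.** Section 2.7.2 (Secondary outcome) defines one rule for four items: "The secondary endpoint is improvement of each item at the outpatient visit at 4 and 8 weeks after Goreisan administration". The items are the VAS, salivary amylase activity, a tongue examination and "Weather information (barometric pressure").

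Section 1.2 gives weather a different role. There, changes in barometric pressure and temperature are something that may affect how pain is perceived, and their association with pain is to be explored. The background in the same section cites epidemiological work in rheumatoid arthritis in which a weather storm worsens pain, "particularly due to a decrease in air pressure 3 days before the pain test".

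Section 2.5 (Study protocol) describes the measurement: "During each outpatient consultation, the weather conditions, such as temperature, humidity, and barometric pressure, should be recorded". Pain is assessed at the same visits, the last of which is described so: "Twelve weeks after the first test, a fourth test will be performed". Between visits, "Patients should also observe, and possibly record, the degree of pain at home". No weather reading to match the home records is stated.

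**The concern.** There are two separate problems.

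**The role of the variable.** An endpoint is something treatment might change. Air pressure is the same whichever arm a patient is in, and it has no better or worse direction. If it were analysed as section 2.7.2 is worded, any difference between arms would reflect chance or the timing of visits.

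**The match between measurement and question.** The exploratory aim concerns changes in weather, and the rationale is about short-term falls in pressure. A reading at each visit gives the level on that day. What is at stake is whether the trial can address its own weather aim in the form it states it. The comparison of Goreisan with standard treatment on the primary endpoint is not at stake.

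**Working it through.** **Step 1: the two roles side by side.**

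| Place in the article | Role of barometric pressure |
|---|---|
| Section 1.2 | A factor that may affect pain; its association with pain is to be explored |
| Section 2.7.2, item 4 | An item whose improvement at 4 and 8 weeks is an endpoint |

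Both cannot hold. Treatment has no effect on air pressure by construction, so the role in section 1.2 is the only one that can be analysed.

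**Step 2: inputs for the measurement question.** The plan gives no figure of its own for the weather analysis. From section 2.2.1: about 90 patients enrolled, and about 82 needed before allowing for dropout of about 10%. From section 2.5: four assessments, read here as baseline and weeks 4, 8 and 12, in line with section 2.7.2.

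**Step 3: number of same-day pairs.**

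- All visits, 90 patients: 90 × 4 = 360
- All visits, 82 patients: 82 × 4 = 328
- Weeks 4 and 8 only, the times named in section 2.7.2: 90 × 2 = 180

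**Step 4: what those pairs could detect.** For a within-patient (repeated-measures) correlation with N patients and k visits, the degrees of freedom are df = N(k − 1) − 1. By Fisher's z, the smallest detectable correlation is r = tanh[(z for alpha + z for power) / √(df − 1)]. With two-sided alpha 0.05 the first term is 1.960; the second is 0.842 for 80% power and 1.282 for 90%.

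| N | k | df | r at 80% power | r at 90% power |
|---|---|---|---|---|
| 90 | 4 | 90 × 3 − 1 = 269 | tanh(2.802/√268) = 0.169 | tanh(3.242/√268) = 0.195 |
| 82 | 4 | 82 × 3 − 1 = 245 | tanh(2.802/√244) = 0.177 | tanh(3.242/√244) = 0.205 |

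The visit readings can therefore support an exploratory analysis of pain against pressure on the same day.

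**Step 5: what those pairs cannot show.** A change over the preceding days needs at least two readings a few days apart. The readings described are about 4 weeks apart. Their differences are 4-week contrasts and carry no measurement of a fall in the days before a pain score. The number of short-term changes measured by the visit readings alone is zero.

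**The case against.** The strongest reply has four parts.

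- The weather aim is only exploratory, and the visits do yield usable same-day pairs. This stands. A reader might infer that the weather question cannot be answered or that there is no usable exposure. Steps 3 and 4 show that this goes too far.
- Weather data may be collected in ways the article does not show. The schedule table is not reproduced, and section 2.7 refers to a supplementary list of items. Visit dates at three known hospitals could also be linked to station records afterwards. This stands too: the statement that weather is read only at visits means only as far as this article states it. It does not make the visit readings a measure of short-term change.
- The three-day lag comes from rheumatoid arthritis background and is not adopted as this trial's own window. That is correct, so it serves here only as an example. The wider point does not depend on three days: the aim is worded in terms of changes.
- Section 2.11 plans no between-arm test of pressure. This limits the harm, but the endpoint definition in section 2.7.2 remains wrong.

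A further tempting reading is that a daily home diary would turn 360 pairs into 84 × 90 = 7,560 and that its absence is a serious loss. The documents do not support that comparison. It assumes a complete diary and no dropout, whereas section 2.2.1 expects about 10%. Daily scores from one patient are likely to be correlated, and patients at one hospital largely share the same weather, so the count overstates the information. Leaving home recording discretionary is a defensible choice for a supplementary measure.

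**Conclusion.** The point holds in two parts. First, listing barometric pressure among items to be improved is an error in the endpoint definition and contradicts section 1.2. This rests on the text alone, and an analysis plan that is not shown could not make the definition correct. Second, the weather measurement described in section 2.5 yields at most about 360 same-day pairs. Those suffice to explore pain against same-day pressure, with a detectable within-patient correlation of about 0.17 to 0.21, but they do not measure the short-term change that the aim and rationale concern.

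The detectable range assumes that all four visits are complete, errors are independent and patients attend on different days. Shared weather within a hospital or missed visits would make it less favourable. The second part also assumes that the article's description of weather recording is complete. The primary endpoint and the sample size are unaffected.

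**What to change.** 1. Remove barometric pressure from the list in section 2.7.2, and define it as an exposure in the exploratory pain-weather analysis.
2. Link each dated VAS score to meteorological-station records: those from clinic visits, and home records where they exist.
3. Derive the pressure and temperature change over a preceding window stated before the data are examined. Three days, as in the background of section 1.2, is one example.
4. Analyse VAS on that change in a mixed model with a patient random effect, labelled exploratory.

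The cost is an edit to the endpoint list and a small amount of linkage by date and place, which can be done after the visits have taken place. A compulsory daily diary would add patient burden; it is optional and not part of the required change.
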